## Abstract

**Introduction:**

Acute ischemic stroke (AIS) is a leading cause of permanent disability in adults and one of the most time-sensitive emergencies in modern medicine. Rapid diagnosis and initiation of thrombolytic therapy, as well as immediate access to mechanical thrombectomy for patients with large-vessel occlusion (LVO), are critical determinants of favorable outcomes. While Mobile Stroke Units (MSUs) – ambulances equipped with computed tomography (CT) imaging – have demonstrated efficacy in improving outcomes, their deployment is often constrained to urban environments due to cost-efficiency considerations. Blood biomarkers offer a potentially cost-effective alternative for stroke diagnosis and subtyping. Especially for patients with LVO, a prehospital biomarker-based identification could enable a streamlined transport strategy directly to thrombectomy-capable stroke centers. In this study, we evaluate the diagnostic accuracy and feasibility of a novel point-of-care test (POCT) in predicting LVO stroke, along with the levels of vascular biomarkers—NT-proBNP, D-Dimer, and H-FABP—from ultra-early whole-blood samples of patients with suspected stroke in a prehospital setting. The test integrates a blood-based multiplex lateral flow assay (LFA) with clinical decision support (CDS) software, accessible through a Mobile Application (App). The study was registered in the German Clinical Trials Register (DRKS-ID: DRKS00037840).

**Methods and analysis:**

This multicenter prospective observational study will include 800 patients with suspected stroke, enrolled within 24 h after symptom onset. Participants will be recruited at three Mobile Stroke Unit (MSU) sites in Berlin, Germany. Prehospital blood samples will be analyzed directly in the ambulance using the LVOCheck device. The test achieves its performance by quantifying the blood levels of the vascular biomarkers (NT-proBNP, D-Dimer, and H-FABP), and inputting these concentrations, along with neurological assessment score and patient-specific medical information such as age and blood pressure, to output predictive information on the probability of LVO stroke, together with all the input data. Additional clinical data, including final diagnoses, will be documented in electronic case report forms (eCRFs). The diagnostic performance of LVOCheck will be evaluated through comprehensive statistical analysis of the combined biomarker and clinical data, including assessment of sensitivity, specificity, and predictive models.

**Discussion:**

This real-world study aims to evaluate the diagnostic accuracy and feasibility (including human factors and usability) of LVOCheck, a portable, non-invasive multiplex POCT at prehospital settings, such as an ambulance, in the prediction of acute LVO diagnosis and triage of suspected acute LVO stroke patients. Utilizing Mobile Stroke Units (MSUs) as recruiting sites enables the analysis of ultra-early biomarker levels from prehospital whole-blood samples combined with patient-specific medical information to provide a predictive risk of LVO stroke. A cost-effective and practical POCT could provide additional biochemical information to support prehospital LVO identification in the future, thereby potentially assisting emergency medical services in transport decisions regarding direct transfer to thrombectomy-capable centers. This may improve triage efficiency, treatment metrics and outcomes in both urban and rural settings.

**Clinical trial registration:**

https://www.drks.de/search/de/trial/DRKS00037840/details, Identifier DRKS00037840.

## Introduction

Neurological diseases, and particularly cerebrovascular conditions like acute ischemic stroke (AIS) are major contributors to global disease burden (1). Due to the low tolerance to hypoxia of brain tissue, stroke is one of the most time-sensitive emergencies in modern medicine. To limit tissue injury, reduce disability, and decrease mortality, effective revascularization therapies like intravenous thrombolysis (IVT) and, in cases of large vessel occlusion (LVO), mechanical thrombectomy (MT) must be administered within established therapeutic time windows after symptoms onset.

Given the time-critical nature of these evidence-based treatments for AIS, they must be initiated at the earliest possible moment following symptom onset and transportation and diagnostic delays must be minimized (2–4). The treatment efficacy of revascularizing therapies is especially impactful, when administered during the critical first hour after onset, known as “golden hour of stroke” (5, 6). The first point of contact for stroke patients after symptom onset typically is the emergency medical team, which may include paramedics and in some countries prehospital emergency physicians depending on the local healthcare system. Despite early first contact with the healthcare system in many cases, treatment is often delayed due to the need for transportation to a stroke-capable hospital and, in cases of LVO, often a secondary transfer to a thrombectomy-capable center. Starting reperfusion therapy later after onset is associated with reduced intervention effectiveness in many cases. This is particularly evident in the near-exponential decline in IVT efficacy observed within the “golden hour” (7). Notably, recent clinical trials have shown how medium and distal-vessel occlusion may not benefit from MT as much as strict LVO cases do, which support the demand of improved screening LVO cases (8, 9).

Mobile Stroke Units (MSUs) are specialized ambulances equipped with computed tomography (CT) scanners, angiography functionality, and point-of-care (POC) testing to allow for immediate stroke diagnosis and prehospital therapy initiation. The use of MSUs reduces alarm-to-treatment times, increases overall intervention rate but particularly within the first hour of symptom onset (“golden hour”), and improves patients outcomes compared to conventional emergency care (5, 10–12). Since 2011, the Berlin Fire Department has implemented three MSUs (Stroke Emergency Mobiles, STEMO), providing a successful model for prehospital stroke management in a metropolitan area (13).

For LVO, MT is the guideline-recommended treatment alongside IVT (3, 4). While IVT is widely available at regional stroke units, the availability of MT is comparatively limited and is restricted to thrombectomy-capable stroke centers.

Current evidence suggests that neither grounding transportation strategies to primary stroke centers (PSC, “Drip-and-Ship”) nor thrombectomy-capable stroke centers (TCSC, “Mothership”) for severely affected patients with suspected LVO, demonstrate significant outcome improvements for either of the groups at a population level (14). However, reliable and early LVO detection outside the hospital setting could improve outcomes by allowing direct transport to TCSCs for select patients. In current practice—particularly in settings without mobile stroke units (MSUs)—prehospital triage for large vessel occlusion (LVO) mainly relies on clinical severity-based tools such as the RACE or LAMS scales. However, these clinical scales have limited diagnostic accuracy for detecting LVO, often leading to both under- and over-triage. As highlighted by Helwig et al. (15), MSU-based imaging triage substantially outperforms such clinical assessments in identifying LVOs, but MSUs currently remain to be economically feasible only in metropolitan regions (16, 17). Thus, reliable and early LVO detection outside the hospital setting remains an unmet need, particularly in non-metropolitan areas. Blood-based biomarkers represent a promising alternative, potentially offering minimally invasive, “easy-to-use,” and economical options for stroke and LVO identification. However, the sensitivity of individual biomarkers is often insufficient for clinical use. Combining multiple biomarkers might enhance the diagnostic accuracy of blood-based tests for stroke and its subtypes. This study focuses on assessing the diagnostic potential of three previously reported biomarkers to enhance the detection of LVO.

N-terminal pro-B-type Natriuretic Peptide (NT-proBNP) is a cleavage product of proBNP, which is primarily expressed by cardiomyocytes and is released into the bloodstream in response to increased myocardial wall stress, as observed in conditions like heart failure. Elevated levels of NT-proBNP are frequently observed in cardioembolic strokes, which often present with LVO (18–20).

D-Dimer is a fibrin degradation product generated during fibrinolysis. It reflects active clot formation and breakdown. Elevated D-Dimer levels have been associated with acute ischemic stroke, particularly in cardioembolic subtypes, and may furthermore correlate with stroke severity and prognosis (21, 22). However, D-Dimer elevation lacks specificity, as levels can be elevated in various conditions (pulmonary embolism, thrombosis, trauma, infection).

Heart-type fatty acid-binding protein (H-FABP) is rapidly released following neurological injury and may help distinguish ischemic stroke from so-called stroke mimics (23). Stroke mimics are a heterogeneous group of diseases (e.g., migraine or seizures), that can present with stroke-like symptoms without evidence of a permanently impaired brain perfusion.

We hypothesize, that the combined assessment of H-FABP, D-Dimer and NT-proBNP with clinical parameters in patients with suspected LVO-stroke can improve prehospital LVO identification.

Historically, stroke biomarker research has focused primarily on measurements of blood samples obtained after hospital admission (24). As a result, insights into the early and ultra-early dynamics of blood-based biomarkers are limited. This limitation may have contributed to the lack of translational success in the field of biomarker research in stroke despite several decades of research. The advent of MSUs now allows to address this limitation.

Studies on the integration of simpler and widely accessible platforms, such as smartphones, for image capture and biomarker analysis, showed promising results with respect to a fast and accurate stroke diagnosis in ambulances and other prehospital environments (25). The LVOCheck technology utilizes an integrative design, which combines a blood-based multi-biomarker single LFA test, with a Mobile Application (App). This integration might provide enhanced predictive capabilities in pre-hospital stroke care, facilitating early and accurate prediction of LVO strokes.

In this study, we aim to evaluate the diagnostic accuracy and feasibility of a novel POCT for predicting LVO stroke within existing stroke care protocols aboard MSUs. The tool integrates clinical data collected by emergency responders with measurements of three vascular biomarkers—NT-proBNP, D-Dimer, and H-FABP—to generate a combined probability score, assisting healthcare providers in pre-hospital prediction and triage of suspected acute LVO stroke patients. This approach facilitates early biomarker assessment directly at the POC, simulating the intended future use case in standard ambulances.

## Methods and analysis

### Aim of the study

The primary aim of this study is to evaluate whether the prehospital, field-based, multiplex POC LVOCheck device, which quantifies the blood levels of three vascular biomarkers—NT-proBNP, D-Dimer, and H-FABP—can effectively assess the risk of an LVO stroke in patients with suspected acute stroke. These biomarker levels, combined with neurological assessment scores and other patient-specific medical information (age and blood pressure), are inputted into a Mobile App to generate a risk estimate. Based on preliminary data, we hypothesize that this approach can achieve a specificity above 92.5% and a sensitivity above 50% for LVO prediction.

The hypothesis will be tested by assessing biomarker levels during the ultra-early prehospital phase in patients suspected of acute stroke, as based on the initial dispatch center telephone triage, regardless of the final diagnosis. Considering that many prior studies have focused on measuring biomarker levels in blood samples collected during later stages of AIS, primarily after hospital admission, the levels of biomarkers in the early prehospital phase of stroke remain largely unexplored.

The study methodology builds upon data from prior investigations, BIO-FAST (26) which was presented at ESOC 2021, as well as the preceding pilot study LVOCheck-Opti (27), which is currently under evaluation. These studies informed the development of lateral flow assays with clinically relevant detection thresholds for the three biomarkers under investigation.

The LVOCheck-Eva study will assess the diagnostic accuracy of the developed POCT tool in real-world conditions. This evaluation will help determine the feasibility (including human factors and usability) of integrating biomarker-based LVO prediction into standard stroke operating procedures for emergency medical services.

Given the rapid progression of neuronal injury after symptom onset, the sensitivity and specificity of the test are expected to improve with increasing time from symptom onset. It is furthermore hypothesized that most false-positive results will occur in non-LVO AIS patients rather than in those with hemorrhagic stroke or stroke mimics.

## Hypotheses

### Primary study hypothesis

We hypothesize that combining POCT-based measurements of NT-proBNP, D-Dimer, and H-FABP with patient-specific clinical data, will enable pre-hospital identification of LVO in suspected stroke patients with a sensitivity of 50% and a specificity of 92.5%.

### Secondary study hypotheses

The POCT biomarker measurements of NT-proBNP, D-Dimer, and H-FABP in whole blood are equivalent to the values obtained in fresh plasma analysis.

Incorporating LVOCheck into prehospital standard of care (SOC) can support triage decision-making, and be effectively integrated into routine clinical workflows, as assessed through qualitative assessment of HCPs feedback.

## Study design

LVOCheck-Eva is a multicenter prospective observational study enrolling patients with suspected stroke within 24 h of symptom onset, identified through initial telephone-based dispatch center evaluation. The study aims to evaluate the sensitivity and specificity of a newly developed multiplex POCT that integrates NT-proBNP, D-Dimer and H-FABP measurements from whole-blood and plasma samples with patient-specific medical data for LVO risk prediction, in a real-world prehospital setting.

## Study population

### Patient recruitment

The study intends to recruit 800 patients suspected of suffering from acute stroke, identified through dispatch center evaluations, between October 2025 and November 2026, at three mobile stroke unit locations in Berlin. These MSUs are staffed and equipped to provide comprehensive prehospital stroke diagnosis and therapy. Initial triage is conducted by the dispatch center of the Berlin Fire Department using a standardized stroke symptom checklist during telephone assessment.

### Inclusion criteria

Participants qualify for inclusion in the study if they meet all the following criteria:

Age ≥ 18 years.Suspected stroke based on the initial fire department dispatch center evaluation.Symptom onset or last known well (if onset time is uncertain) ≤ 24 h.A vascular access has been established as part of routine clinical care.Blood sample collection possible prior to treatment initiation at the ambulance.

### Exclusion criteria

Participants are excluded from the study if they meet any of the following criteria:

Refusal to participate or withdrawal of written consent, either personally or through a legal representative.Blood sampling is not possible for any reason.Unable to perform a full NIHSS evaluation due to clinical status (coma / intubated).Pregnancy.

### Information and consent

Informed written consent is obtained following the completion of emergency treatment aboard the MSU. If patients are unable to provide consent, it is obtained from their legal representative. If immediate consent cannot be obtained during the prehospital emergency intervention, it will be requested later by the study team from the patient or their legal representative.

### Premature withdrawal of a patient from the study

Participation in the study is voluntary. Participants may withdraw from the study at any time, prematurely and without providing a reason, without any impact on their subsequent medical treatment. If a participant declines to participate, any collected samples and associated data will be destroyed. However, once blood samples and data have been anonymized in the regular course of the study, specific destruction or deletion is no longer feasible.

## Endpoints

The LVOCheck-EVA study aims to evaluate an affordable POC test for the early prediction of LVO. The test is intended for prehospital use in standard ambulances to enable accurate prehospital selection and triage of LVO-patients for direct transport to thrombectomy-capable centers, in line with a “targeted mothership” approach. The primary objective of the LVOCheck-Eva subproject is to assess the real-world diagnostic accuracy of the newly developed POCT for estimating LVO probability in patients with suspected acute stroke. The generated data will help to assess the feasibility of integrating this POCT-tool into standard operating procedures for regular ambulances.

### Primary endpoints

The primary endpoint of the study is the accuracy of LVOCheck, integrating patient-specific clinical data and POCT-based measurements of H-FABP, D-Dimer, and NT-proBNP, to predict LVO probability, evaluated against the gold-standard final hospital diagnosis, expressed as sensitivity and specificity.

### Secondary endpoints

The secondary endpoints are divided in three main areas of interest:

First, the study will assess the matrix equivalence between whole blood and plasma samples for NT-proBNP, D-Dimer, and H-FABP measurements using the LVOCheck device.

Secondly, the study will perform a qualitative assessment of the possible future clinical utility of LVOCheck in guiding pre-hospital triage decisions through physician-reported evaluations regarding the impact of individual biomarker concentrations and the overall risk score on clinical decision-making and patient transport strategies.

Finally, the study will evaluate the integration of LVOCheck into clinical workflows through structured collection and analysis of HCPs feedback on practical implementation and compatibility with routine care protocols.

### Safety endpoints

Technical performance evaluated by the frequency and severity of test malfunctions reported through the Mobile App, as well as the rate of critical LVOCheck failures.

The proportion of false-positive assessments (non-LVO patients classified as high-probability LVO) and false-negative assessments (LVO patients not classified as high-probability LVO) by this technology.

## Collection and processing of data and samples

Patients with symptoms of acute stroke receive intravenous access for drug administration, contrast agent application and blood sample collection as part of the clinical routine. Directly after venipuncture, extra samples will be obtained without requiring an additional venipuncture. A small volume (26.9 μL) of whole blood will be dispensed with a U-Pette (LabCon, [name]), directly adjusted to the heparin vacutainer, adding the buffer just after the blood has been completely absorbed for immediate POC testing. After a 10-min incubation, the LFA results are scanned using the Mobile App. The resulting biomarker concentrations from the test are combined with selected clinical parameters (e.g., age, blood pressure, stroke score) for automated processing, and output of the predictive risk of LVO. The cloud component runs on the established and secure Extra Horizon platform^1^, adhering to ISO 27001:2017 and ISO 27701:2019 standards. The results displayed by the Mobile App are directly saved in the communication system WebPortal and additional clinical data are manually entered into the electronic case report form (eCRF) in Research electronic data capture (REDCap) by the treating MSU physician (Figure 1).

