Additionally, patient-specific clinical data is registered by the HCP through the App, including patient ID number, age, blood pressure and neurological scale assessment [to choose between: NIHSS (National Institutes of Health Stroke Scale), Cincinnati (Cincinnati Prehospital Stroke Severity Scale), RACECAT (Rapid Arterial Occlusion Evaluation for CATalonia), G-FAST (Cincinnati Stroke Scale-Modified for Gaze, Face, Arm, Speech, and Tim)]. No data allowing for patient identification is entered into the Mobile App. For study purposes, full NIHSS assessment will be performed through the Mobile App.

Finally, after integrating the biomarker concentrations and patient-specific clinical parameters, the predictive LVO risk is calculated by the software component. The Mobile App temporarily displays output data (biomarker concentrations and LVO stroke risk/probability) alongside the clinical input data (age, blood pressure, stroke assessment score), while simultaneously being transmitted to the WebPortal communication system for secure and long-term storage. Additional clinical information, comprising patient final diagnosis, is documented by the treating physician in the eCRF. Due to the MSU’s specialized staffing structure, brief sample handling, and automated smartphone-based notifications, the proposed POC test integrates seamlessly into routine clinical workflows, allowing patient care to proceed without interruption and without prolonging on-scene time.

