## Statistical analysis

A detailed statistical analysis plan will be provided before the analyses of the data. Descriptive statistics, including mean, standard deviation, median, and interquartile range (IQR), will be reported for key variables such as patient age. Predictions for each patient will be generated using the regression model developed in the previous phase and compared against the confirmed diagnoses to estimate sensitivity, specificity, accuracy, and corresponding 95% CIs. Exploratory subgroup analyses will be conducted to explore potential differences across demographic or clinical strata.

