### Statistical analysis of the primary hypothesis

The definitive diagnosis of LVO as documented in the physician’s letter will serve as the reference standard for the analysis (Comparator). Multiple predictive models will be constructed to estimate each patient’s probability of LVO. Independent variables will include H-FABP, D-Dimer and NT-proBNP, and relevant clinical parameters readily available in the acute setting. The primary goal is to assess whether incorporating biomarker levels measured through POCT along with an LVO prediction diagnostic accuracy beyond what can be achieved with standard clinical information alone. Consequently, models that include both biomarkers and baseline clinical data will be compared against models featuring only clinical data. Key metrics such as sensitivity, specificity, positive predictive value (PPV) and negative predictive values (NPV) will be calculated to assess the diagnostic accuracy in detecting LVO in suspected stroke patients. Receiver Operating Characteristic (ROC) analysis will be used to evaluate overall diagnostic performance, with confidence intervals computed for all metrics to assess precision. Various predictive models will be examined iteratively which sensitivity is maximized while preserving a specificity level of at least 92.5%. This approach will characterize the real-world diagnostic accuracy of the POCT for LVO-prediction.

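### The analysis text does not name the App's stored on-scene LVO probability as the result to be scored, so the primary sensitivity and specificity may describe a model other than the deployed device

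*Protocol article*

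**What the plan says.** The Primary endpoints section defines the target: "The primary endpoint of the study is the accuracy of LVOCheck, integrating patient-specific clinical data and POCT-based measurements", judged against the final hospital diagnosis as sensitivity and specificity. The Endpoints section gives the aim as to "assess the real-world diagnostic accuracy of the newly developed POCT for estimating LVO probability in patients with suspected acute stroke".

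The device sections show that the result to be judged is produced and kept during the call. Under Description of the LVOCheck POCT device, the software calculates the risk, and "The Mobile App temporarily displays output data (biomarker concentrations and LVO stroke risk/probability) alongside the clinical input data", with simultaneous transmission to the WebPortal. Under Collection and processing of data and samples: "The results displayed by the Mobile App are directly saved in the communication system WebPortal". A second test on heparin plasma is documented in the same way. The device section also says that thresholds were set with data from LVOCheck-Opti and BIO-FAST.

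The analysis text takes its predictions from two other sources:

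- Statistical analysis: "Predictions for each patient will be generated using the regression model developed in the previous phase and compared against the confirmed diagnoses".
- Statistical analysis of the primary hypothesis: "Multiple predictive models will be constructed to estimate each patient’s probability of LVO". These models are examined iteratively to maximise sensitivity while specificity stays at 92.5% or more, and the section describes this as characterising the real-world accuracy of the test.

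The abstract's methods paragraph is neutral: "The diagnostic performance of LVOCheck will be evaluated through comprehensive statistical analysis of the combined biomarker and clinical data". Safety endpoints counts false positives and false negatives, the latter being "LVO patients not classified as high-probability LVO", and attributes these classifications to the technology itself.

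**The concern.** In a diagnostic accuracy study, the index result is half of the primary endpoint. Here the natural index result is the probability that the deployed software produced at the patient's side. If the plan is followed as written, the primary 2×2 table is filled from a model run or built at analysis.

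Two things are at stake. First, sensitivity and specificity might characterise an equation that no ambulance crew was shown, while being reported as the accuracy of LVOCheck. Second, the study could publish two false-negative rates for the same LVO patients: one minus the primary sensitivity (from a model) and the safety share (from the device), with nothing in the plan to say why they differ.

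This goes beyond detail left to a later analysis plan. The article states where the scored predictions come from, and neither stated source is identified with the stored output.

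**Working it through.** **1. Reproducing the plan's precision figures.** Inputs from Sample size estimations: N = 800, LVO share 14.4%, sensitivity 75%, specificity 95%.

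- LVO patients: 800 × 0.144 = 115.2. Non-LVO: 800 − 115.2 = 684.8.
- Exact (Clopper-Pearson) limits with x = p·n: lower = Beta⁻¹(0.025; x, n − x + 1), upper = Beta⁻¹(0.975; x + 1, n − x), half-width = (upper − lower)/2.
- Result: 8.26 points for sensitivity and 1.71 for specificity. The plan states 8.26 and 1.7, so its figures reproduce. The Wald formula would give 7.91 and 1.63.

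These numbers are sound. They serve below only as a yardstick.

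**2. Which prediction is scored, section by section.**

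| Section | Source of the LVO prediction |
|---|---|
| Primary endpoints | LVOCheck |
| Collection and processing; Description of the device | App software, on scene, stored |
| Safety endpoints | the technology's own classification |
| Statistical analysis | prior-phase regression model; identity with the App's model not stated |
| Statistical analysis of the primary hypothesis | several models constructed in this study |

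The first three rows point to the device. The last two, which govern the analysis, do not say that they mean the device's output. The last row also differs from the one above it: a model carried over from a previous phase is not a set of models constructed and iterated here.

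**3. What can and cannot drop out.**

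- *Stays in:* sampling, strip, scan and lot-calibration error, because the models use POCT-measured concentrations. Typing errors in age, blood pressure and NIHSS also largely stay, because these are entered through the App and transmitted with the result. The article describes no later re-entry or correction of them.
- *Can drop out:* the App's own risk calculation, the software version in use, and the cut-off deployed with it.
- *Reported elsewhere:* malfunctions and critical failures are a safety endpoint, but are not stated to enter sensitivity or specificity.

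**4. Scale, under an assumed disagreement rate.** The documents give no rate at which stored and regenerated classes differ. Let d be the net share of patients in a group whose class changes from correct to wrong when the stored result replaces the regenerated one. The estimate then falls by d.

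| d (assumed) | Non-LVO patients | Specificity from 95% | LVO patients | Sensitivity from 75% |
|---|---|---|---|---|
| 0% | 0 | 95.0% | 0 | 75.0% |
| 1% | 6.8 | 94.0% | 1.2 | 74.0% |
| 2.5% | 17.1 | 92.5% | 2.9 | 72.5% |
| 5% | 34.2 | 90.0% | 5.8 | 70.0% |

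A net shift equal to the stated half-width needs 0.017 × 684.8 = 11.6, about 12 non-LVO patients, or 0.0826 × 115.2 = 9.5, about 10 LVO patients. Changes in both directions would partly cancel, and the net could run either way.

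**The case against.** The strongest reply is that the analysis text does not exclude the stored output. Saying that predictions come from the prior-phase model may simply describe what the App does, since its thresholds came from the preceding studies. If the App runs that model, applying it again to the stored inputs returns the displayed value apart from software faults, and the concern nearly disappears. The article also promises a detailed analysis plan, where the exact analysis variable would normally be named.

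Much of this stands. A reader might infer that errors of field use are removed from the real-world accuracy. The documents do not support that: concentrations measured on scene and inputs typed on scene still feed the models, and no section mentions data cleaning, a change of App version or retrospective recalibration. A reader might also infer that the plan has chosen to discard the stored result, or that its accuracy will be flattered by a known amount. Neither is stated. The documents also describe a displayed probability, not a displayed class, so applying a cut-off at analysis is not in itself an error.

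The reply does not reach the primary-hypothesis section. Models constructed and iterated in this study are not the App's calculation, yet their performance is presented as the test's real-world accuracy. Nor does any section state that the prior-phase model and the App's model are the same. A later analysis plan could settle this, but it would have to depart from part of the published text to do so.

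**Conclusion.** The point holds in a limited form. The primary endpoint concerns the device, the device's probability is stored, and the analysis sections do not name it as the index result. As written, the primary sensitivity and specificity can omit the App's risk calculation, software version and deployed cut-off, and can differ from the false-result shares under safety.

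The size is unknown. It is zero if the prior-phase model is the App's model, the same cut-off and inputs are used, the software runs without fault, and the newly constructed models are kept out of the primary estimate. Otherwise it depends on a disagreement rate that the documents do not give; the tabulated rates are assumptions. The narrow specificity interval means that a small net disagreement, about 12 of 685 patients, would be as large as the stated margin.

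The conclusion that field errors vanish from the accuracy estimate would go too far, for the reasons given above. The plan should be changed because the correction is cheap and settles what the primary figures describe.

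**What to change.** In Primary endpoints, Statistical analysis and Statistical analysis of the primary hypothesis, state the following:

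1. The primary index result is the LVO probability stored by the App for the first whole-blood test, with inputs as typed on scene and the software version recorded. This also settles which of the two tests per patient counts.
2. It is classified at the threshold fixed before this study. The device section refers to thresholds from the preceding studies without saying whether a cut-off on the probability is among them, so that cut-off should be named.
3. Sensitivity, specificity and the false-positive and false-negative shares under Safety endpoints are all computed from this one result.
4. Regenerated predictions and newly constructed models are secondary, with the frequency at which their classes differ from the stored one reported. The comparison of models with and without biomarkers still needs fitted models. It should be labelled as a question about added value, not as the accuracy of LVOCheck.

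The cost is wording and an export from the WebPortal, which the data storage section restricts to the developer's administrators and which therefore has to be arranged. No new data collection is needed. The possible downside is slightly less favourable accuracy figures.
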